#### Secondary outcome measures

Child’s physiological status using repeated measure scored using the Children’s Emergency Warning Tool (CEWT) (Authors: Royal Children’s Hospital, Queensland Health, unpublished) at two time points: (1) at time of initial call from the referring hospital (*CEWT*_*t*0_); and (2) at time of arrival of the retrieving team at the bedside at the referring hospital (*CEWT*_*t*2_).CEWT is an observation-chart based tool used within hospitals in Queensland. The tool is designed to identify patient deterioration and to trigger appropriate clinical escalations. The tool has nine components: respiratory rate, respiratory distress, Oxygen rate, Oxygen saturation, temperature, heart rate, blood pressure, capillary refill time, and level of consciousness. Observations are charted at the bedside, as with a conventional patient chart. Within each component, observations are translated to a score, on a scale of 1 (best) to 3 (worst). A score of ‘E’ and purple colour coding is used to prompt an emergency response (e.g. a respiratory rate <10 breaths/min, heart rate <60 beats/min or any component of blood pressure <50 mmHg).After each patient assessment, a total CEWT score is calculated by summing the component scores. A range of clinical responses are triggered by both significant negative changes in between-assessment component scores, and by the total CEWT score.Change in diagnosis (*DX*) using repeated measure taken at three time points: (1) at time of initial call to RSQ (*DX*_*t*0_); (2) at time of arrival of the retrieval team at the bedside at the referring hospital (*DX*_*t*2_); and (3) at time of arrival of the retrieval team and retrieved patient back at the PICU (*DX*_*t*5_).Destination of retrieved patients at the tertiary hospital (i.e. general ward vs. PICU).Retrieval decision (retrieval conducted/not conducted)PICU LoS for retrieved patients.

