### Objectives and hypotheses

#### Hypotheses

Consultation using real-time video-based telemedicine between a PICU consultant and a referring hospital clinician will:Clinical effectivenessReduce the time needed by the retrieval team to stabilise the child before transportImprove the child’s condition between time of initial call and time of retrieval team arrivalReduce diagnostic discordanceReduce the number of retrieved children being admitted to general wards at the tertiary hospitalReduce PICU LoS for retrieved childrenEconomic effectsFrom the health service perspective, be economically beneficial by reducing the number, and consequently the cost, of (i) retrievals, (ii) unnecessary tertiary hospital admissions, and (iii) LoS.

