### Study site selection

The study is funded to provide the RCH PICU and four study sites with telemedicine equipment. To maximise recruitment within the resource constraints of the project, retrospective data were examined to identify four referring hospitals which consistently contributed to the PICU retrieval workload over two recent years (2010, 2011). For this period, when referring hospitals were ranked by retrieval activity, the top four hospitals accounted for 220 patients (i.e. approximately 110 patients per year). These cases represent almost half of the total retrieval workload of the PICU. These study sites are all large regional public hospitals, each with an emergency department, paediatric ward and paediatricians on staff. In some cases, adult ICUs at the referring hospitals may admit paediatric patients if needed. Site round trip distances from the RCH PICU range from 62 km to 1042 km (Table 1). The four sites identified will be provided with telemedicine links to the RCH PICU.

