### Randomisation

Generation of intervention/control arm allocation sequences will occur centrally. Sequences will be generated using permuted block randomisation, with random block sizes of 6,8 or 10 entries and a 1:1 allocation ratio using an online true random number generation service [19]. The process of generating these sequences will be conducted by an independent party. Four tables of random numbers will be generated, one for each study site. Odd numbers will denote allocation to the control arm and even numbers to the intervention. The tables will be held securely on a server on a private network.

A password-protected custom application (accessible by computer or portable device), driven by the random number tables, will be provided for the PICU clinicians to determine cases and controls at time of initial retrieval call from RSQ. The application will record all accesses and allocations.

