**Table 2 Tab2:** **Statistical analyses for each outcome measure**

**Outcome measure**		**Statistical Method**
P1	Stabilisation time^1^	Linear regression with stabilisation time as the outcome, type of consultation as the main effect and PIM3 score as a co-variable
S1	Change in patient’s physiological status	Linear mixed effects model with physiological status as outcome, type of consultation and time as main effects, and a consultation-by-time interaction term.
S2	Change in diagnosis	Logistic mixed effects model with diagnosis as outcome, type of consultation and time as main effects, and a consultation-by-time interaction term.
S3	Destination of retrieved patients	Logistic regression with destination as outcome and type of consultation as the main effect.
S4	Retrieval decision	Logistic regression with retrieval decision as outcome and type of consultation as the main effect.
S5	PICU LoS^1^	Linear regression with LoS as the outcome, and type of consultation as the main effect.

^1^Data relating to stabilisation time and PICU LoS will transformed if necessary to meet assumptions of regression model.

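### S1's follow-up CEWT exists only if a retrieval team arrives, so children not retrieved have no score and the comparison carries a selection bias of unknown size

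*Protocol article*

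**What the plan says.** In the Protocol article, Secondary outcome measures, S1 is CEWT at two times: "at time of initial call from the referring hospital" (t0) and "at time of arrival of the retrieving team at the bedside at the referring hospital" (t2). No other time is given for a child to whom no team is sent. The same list makes destination and PICU length of stay outcomes of retrieved patients, but puts no such limit on S1. It also makes the retrieval decision, carried out or not, an outcome of its own (S4).

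Under Randomisation, the allocation application is used "to determine cases and controls at time of initial retrieval call from RSQ", so a child enters the trial before it is known whether a team will reach the bedside. Under Hypotheses, telemedicine is expected to "be economically beneficial by reducing the number, and consequently the cost, of (i) retrievals".

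Data analysis adopts intention to treat. Table 2 gives the S1 method as "Linear mixed effects model with physiological status as outcome, type of consultation and time as main effects, and a consultation-by-time interaction term". On the tool itself, the protocol says "Observations are charted at the bedside, as with a conventional patient chart".

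**The concern.** Whether the S1 outcome can be observed depends on a later event, retrieval, which the trial expects the intervention to change. A child whose condition improves after the consultation is a natural candidate for not being retrieved, and is also the child who best shows the benefit that S1 is meant to detect. If such children leave the comparison, and more of them leave the telemedicine arm, the arms at t2 are no longer the groups that were randomised.

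The mixed model keeps these children's t0 scores. That is enough only if, given arm and t0 score, the decision not to retrieve is unrelated to how the child went on to do. Improvement after the call that no study score records breaks that condition. At stake is one named clinical hypothesis, that telemedicine improves the child's condition before the team arrives. The primary outcome needs a team by its nature. S1 does not.

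**Working it through.** **1. What the planning figures imply about non-retrieval.** Sample size gives SD 41 minutes, difference 18 minutes, 80 per arm and alpha 0.05 (taken as two-sided). The standard error is 41 × √(2/80) = 6.48. Then 18/6.48 − 1.96 = 0.82, which gives power of 79.3%, so the stated 80% is reproduced. It uses all 80 children per arm as having a stabilisation time, so no allowance is made for non-retrieval. The 20% attrition covers consent and clinician override only. Study site selection gives 220 retrieved patients from the four sites over two years, and Sample size expects 200 retrieval calls in 24 months. Planned calls do not exceed past retrievals, which suggests that few non-retrievals were foreseen. No rate is stated.

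**2. Size when both arms follow the same retrieval rule.** The protocol gives no CEWT SD, effect, correlation or retrieval rule, so everything here is assumed. Later score = 0.6 × t0 score − 0.30 × telemedicine + noise, in SD units, lower being better. A child is retrieved if an index exceeds a cut-off that leaves the stated share of control children not retrieved. The estimate is the likelihood (missing at random) one, from regressing the later score on t0 score and arm in retrieved children. Attenuation = (0.30 − |estimate|)/0.30.

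| Index that decides retrieval | 10% control not retrieved | 20% | 30% |
|---|---|---|---|
| Later score, noise SD 0.5 | -0.247 (18%) | -0.219 (27%) | -0.201 (33%) |
| Equal weight on t0 and later score, noise SD 0.5 | -0.283 (6%) | -0.274 (9%) | -0.265 (12%) |
| Weights 0.7 on t0 and 0.3 on later score, noise SD 0.7 | about -0.30 to -0.29 across the three rates (about 1 to 3%) | | |

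In the first row, non-retrieval in the telemedicine arm is 16%, 28% and 40%. At 5% control non-retrieval, the first rule gives -0.265 (12%). At 2 to 5%, the equal-weight rule gives -0.294 to -0.289. For scale, the standard error with 80 per arm and residual SD √(1 − 0.36) = 0.8 is 0.8 × √(2/80) = 0.13.

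**3. Direction under other rules.** A second set of simulations used correlation 0.5 and the same true effect of -0.30.

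| Rule | Not retrieved, control / telemedicine | Mixed-model estimate |
|---|---|---|
| Improvers not retrieved, same rule in both arms | 19–20% / 25–27% | -0.25 to -0.21 |
| t0 score only | 19% / 19% (or 33%) | -0.30 |
| At random | 10% / 25% | -0.30 |
| Improvers stood down in telemedicine arm, at random in telephone arm | 10% / 32% | -0.04 |
| Improvers stood down in telephone arm, at random in telemedicine arm | 26% / 10% | -0.51 |

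With a true effect of zero, the common rule gives 0.00. The fourth rule gives +0.22, an apparent harm.

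**The case against.** A reader might infer that S1 is biased toward zero, by as much as a third. The documents do not support that as fact. They state no retrieval rule and no non-retrieval rate, and the second table shows that the bias can be nil, away from zero or a false harm. The 18 to 33% figures come from a rule resting almost wholly on the later score. A decision made around the consultation would draw heavily on status at the call, which t0 CEWT records and the model uses. At the low rates that the planning figures suggest, the distortion may be small beside a standard error of 0.13. This stands, and it limits the claim to a bias of unknown size.

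A reader might also infer a bias from the unequal t0 to t2 interval, since "Site round trip distances from the RCH PICU range from 62 km to 1042 km". These are distances by different modes of transport, not times, and allocation is blocked separately within each site. The interval is therefore balanced between arms by design and is not itself a source of bias.

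One could replace t2 by a single fixed time for all sites. That departs from the stated hypothesis, which runs from the call to the team's arrival, and at near sites it could take in the team's own treatment. This objection stands, and the fix below avoids it.

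Handling of missing scores is commonly left to the analysis plan. Here, however, the score is undefined because the event that times it never happens, and an analysis model cannot supply it. Figures 1 and 2 could not be read here and might show how non-retrieved children are treated. The text does not.

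**Conclusion.** The point holds as a defect in how S1 is defined. Its second score depends on a post-randomisation outcome that the trial expects telemedicine to alter, so S1 as written cannot deliver the intention-to-treat comparison that the protocol promises, and the mixed model repairs this only in part. Bias toward zero is the likely direction if telemedicine both improves the child and avoids retrievals because of that improvement, but it is not established. The range of about 1 to 33% rests on the assumed effect, correlation, common retrieval rules and 10 to 30% control non-retrieval. None of these comes from the protocol, and the actual rate may be lower. The outcome is secondary and the repair is inexpensive, so the change should be made.

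**What to change.** Keep CEWT at t2 for retrieved children. For each randomised child not retrieved, take the bedside-charted CEWT nearest to that site's usual interval from call to team arrival, set in advance and applied identically in both arms. S1 then covers every randomised child. Report the comparison in retrieved children alone as supportive.

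Compare arms on follow-up CEWT with t0 CEWT as covariate and site, the unit within which allocation is blocked, in the model. With complete pairs and an assumed correlation of 0.6, this also lowers the variance relative to the change-score contrast given by the interaction term: 1 − 0.36 = 0.64 against 2 × (1 − 0.6) = 0.80.

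The cost is one further chart value for each non-retrieved child. Data collection names the retrieval form, and the patient chart only for diagnosis and tertiary admission location. Extraction of CEWT from referring-hospital charts would therefore have to be added as a source. The protocol does not say how often CEWT is charted or for how long after the call, so a later score may be missing for some children. Their number by arm should be reported, with a sensitivity analysis for the missing scores.

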### Sample size

In this study, resources limit the number of study sites to four and the study duration to 24 months. It is estimated that during the study period there will be 200 retrieval calls relating to eligible participants. We estimate an 80% participation rate (20% attrition due to lack of consent or clinicians electing not to consult by telemedicine and continuing by telephone) and consequently estimate the study will recruit a total of 160 retrieval participants with 80 in each arm. Retrospective stabilisation time data for the study sites showed a standard deviation of 41 minutes. With alpha = 0.05 we have 80% power to detect a clinically important difference in stabilisation time between-consultation types of 18 minutes or greater.

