## Discussion

As specialist care becomes more centralised and the cost of providing care increases, telemedicine may be a way to improve outcomes in a cost-effective way. However, little is known about the use of telemedicine in the complex, risky and expensive area of paediatric acute care retrieval.

Using a pragmatic randomised design, with telemedicine consultation as the intervention and telephone consultation as the control, this study will provide new information on the effectiveness and economics of using telemedicine for paediatric acute care retrieval management in a regionalised public health care system. In particular, it will determine whether using telemedicine for specialist consultation prior to patient retrieval results in a more stable patient and hence lead to their more efficient evacuation to definitive care. It will also examine whether the use of telemedicine improves diagnosis, can improve the appropriateness of retrieval and reduce the length of stay in PICU. The study incorporates an economic analysis to allow the observed effects of telemedicine to be costed.

The results of the study will be useful to both clinicians and health service policy makers in the Australian context and in other regionalised or centralised specialist health care systems.

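### Destination of retrieved children (S3) has no unambiguous favourable direction: the hypothesised improvement in condition can push it against telemedicine, and its denominator is itself an outcome

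*Protocol article*

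**What the plan says.** The Secondary outcome measures section of the protocol article defines S3 as "Destination of retrieved patients at the tertiary hospital (i.e. general ward vs. PICU", so it is binary and confined to children who were retrieved. Table 2 gives the analysis: "Logistic regression with destination as outcome and type of consultation as the main effect". There is no severity term and no link to the retrieval decision.

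The Hypotheses section states the direction. Telemedicine is expected to lower the number of retrieved children who go to general wards at the tertiary hospital. The same list expects it to leave the child in better condition by the time the team reaches the bedside. The economic hypothesis expects gains from "reducing the number, and consequently the cost, of (i) retrievals, (ii) unnecessary tertiary hospital admissions".

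The Discussion carries both ideas forward. It asks whether telemedicine "results in a more stable patient and hence lead to their more efficient evacuation to definitive care", and whether it "can improve the appropriateness of retrieval and reduce the length of stay in PICU". A separate secondary outcome, S4, is "Retrieval decision (retrieval conducted/not conducted".

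**The concern.** Two hypothesised benefits act on the same binary outcome in opposite directions. If telemedicine prevents retrieval of children who would have gone to a ward, the ward share among retrieved children falls. If it improves children so that some who would have needed PICU can go to a ward, the ward share rises. S3 cannot tell a ward admission that reflects an avoidable retrieval from one that reflects recovery before transfer.

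The converse also holds. If the consultation left children sicker and more of them needed PICU, the ward share would fall and S3 would look favourable.

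S3 is also computed only in retrieved children, while retrieval is decided after randomisation and is itself expected to change. The S3 comparison is therefore not between the groups as randomised. At stake is a secondary result that could be reported as no benefit, or as harm, when the intervention did what was hoped, or the reverse.

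**Working it through.** **The plan's own figures.** None is given for S3. The only power statement concerns stabilisation time. It reproduces: with 80 per arm, a difference of 18 minutes, SD 41 and two-sided alpha 0.05 (sidedness assumed), the standard error is 41 × √(2/80) = 6.48, and 18/6.48 − 1.96 = 0.82, giving power of 79.3% against the stated 80%. Nothing below depends on it.

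**Inputs for S3.** The definition, direction and model are those quoted above. The article gives no ward, PICU or non-retrieval rates, so every rate here is an assumption.

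**General condition.** Among control children who are retrieved, let w be the ward share. Under telemedicine, let a be the fraction of ward-bound retrievals that are avoided, and b the fraction of PICU-bound children who improve enough to go to a ward.

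- Control ward odds: w / (1 − w)
- Telemedicine ward odds: [w(1 − a) + (1 − w)b] / [(1 − w)(1 − b)]

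Setting these equal gives w(1 − a) + (1 − w)b = w(1 − b), hence **b = w × a**. At that value the S3 odds ratio is exactly 1 although both benefits are present. Above it, the odds ratio exceeds 1 and reads as harm.

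| Control ward share w | Cancelling b if a = 25% | Cancelling b if a = 50% |
|---|---|---|
| 10% | 2.5% | 5% |
| 20% | 5% | 10% |
| 30% | 7.5% | 15% |

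**Illustration per 100 calls (assumed figures).** The odds ratio compares ward with PICU against control.

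| Scenario | Not retrieved | Ward | PICU | Ward share of retrieved | Odds ratio |
|---|---|---|---|---|---|
| Control | 10 | 18 | 72 | 18/90 = 20.0% | – |
| A: half of ward retrievals avoided | 19 | 9 | 72 | 9/81 = 11.1% | (9/72)/(18/72) = 0.50 |
| B: nine children improve from PICU to ward | 10 | 27 | 63 | 27/90 = 30.0% | (27/63)/(18/72) = 1.71 |
| A and B together | 19 | 18 | 63 | 18/81 = 22.2% | (18/63)/(18/72) = 1.14 |
| C: nine ward-bound children deteriorate and go to PICU | 10 | 9 | 81 | 9/90 = 10.0% | (9/81)/(18/72) = 0.44 |

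Scenario C, a harm, looks at least as good on S3 as scenario A, a benefit. With A and B together, the three-category row shows nine fewer retrievals and nine fewer PICU admissions per 100 calls. S3 shows neither.

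**Precision.** Scaling A and B together to 80 per arm gives 14.4 ward and 50.4 PICU with telemedicine, against 14.4 and 57.6 in control. The standard error of the log odds ratio is √(1/14.4 + 1/50.4 + 1/14.4 + 1/57.6) = 0.42, so the approximate 95% interval around 1.14 is 0.50 to 2.60. In a trial of this size the practical result would be an uninformative null rather than a demonstrable reversal.

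**The case against.** Several objections carry weight.

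- **The key reading is inferred.** A reader might infer that the protocol defines a ward destination as an unnecessary retrieval. It does not say so. The phrase about unnecessary admissions belongs to the economic hypothesis and is not tied to ward destination. That an improved child is more likely to go to a ward is plausible but also unstated. This stands, and it limits the point to ambiguity of direction.
- **S3 is not the sole support for a conclusion.** A reader might infer that the finding on appropriateness of retrieval rests on S3. The Discussion ties it to no single outcome. S4 has its own analysis, and S1 (CEWT at the initial call and at team arrival) is where a worsening condition should appear. This stands.
- **A ward transfer after improvement is not clearly a success.** By the Study site selection section, each referring hospital has its own children's ward and staff paediatricians, so such a transfer might still have been avoidable. This is fair, but it confirms that the outcome has no clear favourable direction.
- **The rates are assumed.** A reader might infer that S3 will cancel. The documents support only that it can. On the count of ward admissions, which is how the hypothesis is worded, the combined example is 18 against 18, a null. The odds ratio above 1 comes from the smaller retrieved denominator (81 against 90).
- **Joint reading could be left to the analysis plan.** S3 and S4 together already hold the information. But the article itself fixes the direction, the binary definition, the restricted population and the model. Added detail elsewhere would not remove the directional hypothesis.

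**Conclusion.** The point holds as one of interpretation and design for a secondary outcome. No stated figure is wrong. S3 as defined has no unambiguous favourable direction, and it is conditioned on a post-randomisation outcome. It can be null or reversed when telemedicine helps, and favourable when children are sicker.

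The size cannot be known from the documents. Under assumed control ward shares of 10–30% and avoidance of 25–50% of ward retrievals, a shift of 2.5–15% of PICU-bound children to the ward is enough for an odds ratio of 1. The conclusion rests on two inferences: that fewer ward admissions are wanted because they stand for avoidable retrievals, and that improvement makes a ward destination more likely. The primary conclusion on stabilisation time is unaffected.

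**What to change.** 1. In the Hypotheses section, drop the statement that fewer ward admissions among retrieved children is in itself the benefit.
2. In Table 2, replace row S3 with a three-category outcome (not retrieved, retrieved to ward, retrieved to PICU) compared by arm over all randomised children, with counts and percentages per category. This restores the randomised denominator.
3. State that the result will be interpreted together with S1, in particular CEWT at team arrival (t2), and with S4.

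Do not add rules that attribute shifts between categories to a cause, such as crediting avoided retrievals only if the ward share falls as non-retrieval rises by the same amount, or crediting improvement only if non-retrieval is unchanged. In the combined example (19/18/63 against 10/18/72) such rules would credit neither benefit. The same row would also arise if nine PICU-bound children were simply not retrieved. The table shows the net changes by arm but cannot say why individual children moved.

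The cost is small: one hypothesis, one row of Table 2 and one results table. Retrieval decision and destination are already collected. The downside is that S3 is no longer summarised by a single odds ratio.
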